### Sub-Study Sample Size

Thirty-three participants per group are required to detect an absolute minimum difference in PCr/ATP ratio of 0.37 between ECM expansion and no ECM expansion groups at baseline (80% power, 5% significance level, 2-sided), assuming a standard deviation of the between group differences of 0.52, as per Phan [52]. This effect size is based on that seen in previous studies [52, 54]. Twenty-six participants per group are required to detect an absolute minimum difference, between pirfenidone and placebo groups, of 0.4 in terms of absolute change in PCr/ATP ratio from baseline following 52 weeks of treatment (80% power, 5% significance level, 2-sided), assuming a standard deviation of the within-patient differences from baseline equal to 0.5, as per Beadle [55]. This effect size is based on that seen in other studies [54–57]. In order to allow for a potential 20% drop out prior to final scan at 52 weeks, the number scanned at baseline will be inflated to 33 per group.

### Analysis

The trial will be analysed and reported using the ‘Consolidated Standard of Reporting Trials’ (CONSORT) and the International Conference on Harmonisation E9 guidelines. All primary analyses will be on an intention to treat basis including all randomised participants retained in their randomised treatment groups. Secondary causal analyses (according to dose and duration of intervention) will also be undertaken to assess the causal impact of treatment received. Analyses of covariance will be used to compare myocardial ECM volume (and other measures) between pirfenidone and placebo groups, adjusting for baseline ECM volume. The conventional 5% significance level will be used.

For the sub-study, PCr/ATP ratio and mechanical variables will be compared between patients with and without ECM expansion at baseline using an independent *t* test assuming the measurements are normally distributed, with transformation as necessary. Correlation analysis will be used to assess the relationships between PCr/ATP ratio, mechanics and ECM volume. PCr/ATP ratio will be compared between pirfenidone and placebo groups using analyses of covariance, adjusting for baseline PCr/ATP ratio.

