### Study Objectives

The primary objective of this study is to evaluate whether pirfenidone compared to placebo leads to regression of myocardial fibrosis in patients with HFpEF and myocardial fibrosis. The secondary objectives are to determine the efficacy of pirfenidone compared to placebo with regard to improving ventricular structure and function, left atrial volume and function, aortic function, myocardial energetics, circulating markers of fluid status and myocardial injury, exercise tolerance and quality of life in patients with HFpEF and myocardial fibrosis. The study will also evaluate the safety of pirfenidone in patients with HFpEF and compare it to that of placebo, and record screening and recruitment data in order to inform a subsequent phase III study. Outcome measures are listed in full in Table 1.

**Table 1 Tab1:** Primary and secondary outcome measures

Primary outcome	
Absolute change in myocardial ECM volume, measured using CMR, from baseline to week 52.	
Secondary outcome measures	
(a) Absolute change in LV and RV mass, volumes, ejection fraction and tissue characteristics from baseline to week 52, measured using CMR. (b) Absolute change in absolute myocardial ECM volume from baseline to week 52, measured using CMR.* (c) Absolute change myocardial cell volume from baseline to week 52, measured using CMR.* (d) Absolute change in LV diastolic function, strain, backscatter and torsion from baseline to week 52, measured using echocardiography. (e) Absolute change in LA and RA volume, and LA function from baseline to week 52, measured using CMR. (f) Absolute change in pulse wave velocity and aortic distensibility from baseline to week 52, measured using CMR. (g) Absolute change in myocardial energetic status (PCr/ATP ratio) from baseline to week 52, measured using ^31^P MRS. (h) Absolute change in NT-proBNP, and HS-troponin T from baseline to week 13, baseline to week 26 and baseline to week 52. (i) Absolute change in exercise tolerance from baseline to week 52, measured using 6-min walk distance. (j) Absolute change in health status (quality of life), HF symptoms and physical limitations from baseline to week 52, measured using change in KCCQ score. (k) All-cause mortality, cardiovascular mortality and hospitalisation for heart failure will be recorded but the trial is not powered for these clinical outcomes.	
Safety outcome measures	

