## Statistical Considerations

### Sample Size

Thirty-seven participants per group are required to detect an absolute minimum difference, between pirfenidone and placebo groups, of 2% in terms of change in CMR ECM volume from baseline following 52 weeks of treatment, with 80% power at a 5% significance level (2-sided), assuming a standard deviation of the within-patient differences from baseline equal to 3%, as per Garg et al. [53]. This effect size is based on a conservative estimate of the magnitude of ECM regression that is expected to translate into improved clinical outcomes, based on the magnitude of histological collagen regression (3.6% absolute reduction) seen with 52 weeks of treatment with losartan, a medication known to improve clinical outcomes in patients with HF with reduced ejection fraction, in patients with hypertensive heart disease and baseline ECM expansion [25]. To allow for treatment discontinuation in up to 20% of participants prior to final follow-up, the number randomised to each group will be inflated to 47. This discontinuation rate is in keeping with the proportion of patients who discontinued pirfenidone prematurely, at the same target dose as here, in the trials in pulmonary fibrosis [35–37]. Therefore, 94 participants are required to undergo randomisation. In the previously described study by Schelbert el al, 63% of patients with HFpEF had an ECM volume ≥ 27% [22]. Thus, and in order to allow for variation in the proportion of participants with an ECM volume ≥ 27%, it is anticipated that up to 200 patients may need to be recruited to undergo baseline assessment.

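### Read literally, the ANCOVA rule adjusts the non-ECM continuous secondary outcomes for baseline ECM volume and not for their own baselines, which costs precision

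*Protocol article*

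**What the plan says.** The Analysis section of the protocol article has one sentence on how the two arms are compared: "Analyses of covariance will be used to compare myocardial ECM volume (and other measures) between pirfenidone and placebo groups, adjusting for baseline ECM volume". It sets the test level in a separate sentence: "The conventional 5% significance level will be used".

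The sub-study paragraph of the same section gives a separate rule for the energetics outcome: "PCr/ATP ratio will be compared between pirfenidone and placebo groups using analyses of covariance, adjusting for baseline PCr/ATP ratio".

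Table 1, under Study Objectives, defines the continuous secondary outcomes as absolute changes from baseline. Item (i), for example, is "Absolute change in exercise tolerance from baseline to week 52, measured using 6-min walk distance", and item (g) is "Absolute change in myocardial energetic status (PCr/ATP ratio) from baseline to week 52". Item (k) is of a different kind: "All-cause mortality, cardiovascular mortality and hospitalisation for heart failure will be recorded but the trial is not powered for these clinical outcomes".

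The baseline values exist. Baseline Evaluations lists laboratory tests, CMR, echocardiogram, walk test and KCCQ at the first visit, and Safety Monitoring and Follow-up repeats the baseline procedures at week 52 to assess the outcomes.

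**The concern.** For a continuous outcome measured before and after treatment, its own baseline is usually the most useful covariate. The general sentence names a different one. For walk distance, KCCQ, NT-proBNP, troponin and the structural and functional measures, no other rule is given.

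This is not a detail left to the analysis plan: a covariate is stated, and for these outcomes it is a less efficient choice. An analysis plan that follows the sentence inherits the loss, and one that uses each outcome's own baseline departs from the published text.

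At stake is the precision of the outcomes meant to show whether fibrosis regression brings gains in cardiac structure and function, fluid status and quality of life. About 37 evaluable patients per arm are planned, and randomisation is stratified by sex only. A chance imbalance in, say, baseline NT-proBNP is therefore plausible, and adjustment for ECM volume alone would largely leave it in the estimate.

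**Working it through.** **1. The plan's own figures reproduce.** Inputs from Sample Size: an "absolute minimum difference, between pirfenidone and placebo groups, of 2"% in change, SD of change 3%, "with 80% power at a 5% significance level (2-sided").
- Normal approximation: n = 2 × (1.960 + 0.842)² × (3/2)² = 2 × 7.849 × 2.25 = 35.3, so 36 per group. The exact two-sample t-test needs 37, as stated.
- Inflation: 37/0.8 = 46.25, so 47 per group and 94 in total, as stated.
- Sub-study change in PCr/ATP (difference 0.4, SD 0.5): 2 × 7.849 × (0.5/0.4)² = 24.5, so 25. The t-test needs 26, as stated, and 26/0.8 = 32.5 gives 33.

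None of this depends on the covariate wording. The primary outcome is already adjusted for its own baseline.

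**2. Which outcomes the wording reaches.**
- Reached: LV/RV measures (a), echocardiographic measures (d), atrial measures (e), aortic function (f), NT-proBNP and HS-troponin T (h), 6-minute walk (i), KCCQ (j).
- Not reached: PCr/ATP (g), which has a specific own-baseline rule, and the events in (k), which are not ANCOVA outcomes.
- Left aside: absolute ECM volume (b) and cell volume (c), whose calculations are in an appendix not shown.

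**3. Size of the loss.** Assume equal outcome variance (set to 1) at baseline and week 52. Let ρ be the correlation of an outcome's baseline with its own week-52 value, and c the correlation of baseline ECM with the variable analysed. The documents give neither ρ nor c. Residual variances are:
- own-baseline ANCOVA: 1 − ρ²
- change score adjusted for ECM only: 2(1 − ρ)(1 − c²)
- week-52 value adjusted for ECM only: 1 − c²

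With c = 0, the variance of the treatment effect relative to own-baseline ANCOVA is 2(1 − ρ)/(1 − ρ²) = 2/(1 + ρ) for the change score and 1/(1 − ρ²) for the week-52 value.

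| ρ | Change score | Week-52 value |
|---|---|---|
| 0.3 | 2/1.3 = 1.54 | 1/0.91 = 1.10 |
| 0.5 | 2/1.5 = 1.33 | 1/0.75 = 1.33 |
| 0.7 | 2/1.7 = 1.18 | 1/0.51 = 1.96 |
| 0.8 | 2/1.8 = 1.11 | 1/0.36 = 2.78 |
| 0.9 | 2/1.9 = 1.05 | 1/0.19 = 5.26 |

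If ECM is correlated with the change, the change-score ratio is multiplied by (1 − c²). At c = 0.3 it becomes 1.33 × 0.91 = 1.21 at ρ = 0.5, 1.07 at ρ = 0.7 and 0.96 at ρ = 0.9, where the penalty has gone.

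**4. In terms of power.** Take 37 per arm, an assumed effect of 0.5 SD of the outcome, c = 0, two-sided 5%, noncentral t with 71 degrees of freedom. At ρ = 0.5 the residual SD is √0.75 = 0.866 with own baseline and 1 for the change score. The noncentrality is 0.5/0.866 × √(37/2) = 2.48 against 2.15, and power is about 69% against 56%. At ρ = 0.7 it is about 84% against 78%, and at ρ = 0.8 about 94% against 92%.

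**The case against.** The strongest reply is that the sentence is shorthand. It is written around the primary outcome, with the other measures in a bracket. The one place where the article spells out the model for a non-ECM outcome, the PCr/ATP sentence, uses that outcome's own baseline. The authors may well intend this throughout, and a condensed article need not list covariates outcome by outcome. That is plausible and lowers the severity. It does not dispose of the point, because the text names a specific covariate and the reader has to guess that another is meant.

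Four stronger readings are tempting, and the documents do not support them.

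- **The plan contradicts itself on PCr/ATP.** PCr/ATP is secondary outcome (g), so a reader might see two models for one comparison. But it has its own sub-study, sample size and analysis sentence, and a specific rule ordinarily overrides a general one. An analyst would have little doubt which to use.
- **Every other outcome is affected.** PCr/ATP and the clinical events are not.
- **The estimates would be biased.** Under randomisation, a change-score comparison adjusted for baseline ECM volume is unbiased on average. Chance baseline imbalance and regression to the mean affect the single realised estimate, which is the precision point again.
- **The loss is large.** The biggest ratios come from analysing week-52 values. Table 1 defines these outcomes as changes, so that is the less natural reading, although the Analysis sentence speaks of comparing the measures themselves. On change scores the loss is modest and shrinks as ρ rises.

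**Conclusion.** The point holds on the literal wording and for the continuous secondary outcomes not based on ECM. Its consequence is loss of precision only. For change scores with c = 0, the variance of the treatment effect is about 33%, 18% and 5% higher than with own-baseline ANCOVA at ρ = 0.5, 0.7 and 0.9. If week-52 values were analysed, the corresponding increases would be about 33%, 96% and over 400%.

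These sizes rest on assumed values of ρ and c and on equal variances. The loss on change scores is smaller if baseline ECM predicts the change. The direction is secure except where ρ is high and ECM is also a useful predictor. Severity is minor to moderate.

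**What to change.** In the general ANCOVA sentence, replace the closing covariate phrase with: *adjusting for the baseline value of the outcome being analysed (baseline ECM volume for the primary outcome)*. This matches the existing PCr/ATP sentence, which can stand unchanged. Baseline ECM volume may be kept as an additional covariate if wanted.

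Once an outcome's own baseline is in the model, analysing the change or the week-52 value gives the same treatment effect, so the difference in wording between Table 1 and the Analysis section stops mattering.

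A sex term, prompted by the stratification, is a separate question. Added to this sentence alone, it would leave PCr/ATP with two covariate sets.

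The cost is one phrase. No new data are needed and the sample size does not change. If the analysis plan already specifies own-baseline adjustment, only the published wording needs to be aligned with it.

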#### Randomisation

After confirmation of eligibility, participants are randomised in a 1:1 ratio to double-blind treatment with either pirfenidone or placebo. Randomisation is done using web randomisation software accessed using a secure website provided via the Clinical Trials Unit. Block randomisation, stratified by sex (because ECM volume is higher in females than males), is implemented, with computer generated randomisation allocations.

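### Randomisation is stratified by sex, but the stated ANCOVA does not name sex as a covariate; adding it costs one degree of freedom and may recover a little precision

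*Protocol article*

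**What the plan says.** The Randomisation section gives both the stratification factor and the reason for it: "Block randomisation, stratified by sex (because ECM volume is higher in females than males), is implemented". Allocation is equal between the arms.

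The primary outcome in Table 1, under Study Objectives, is "Absolute change in myocardial ECM volume, measured using CMR, from baseline to week 52". The Analysis section compares ECM volume and other measures by analysis of covariance "between pirfenidone and placebo groups, adjusting for baseline ECM volume". No other covariate is named, and sex does not appear in that section. For the sub-study, the comparison of PCr/ATP ratio between arms is an ANCOVA on baseline PCr/ATP ratio, again without sex.

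The Sample Size section asks for 37 evaluable participants per group to detect a 2% difference in change with 80% power at a two-sided 5% level, "assuming a standard deviation of the within-patient differences from baseline equal to 3"%. It is inflated to 47 per group, 94 in all, for 20% discontinuation.

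**The concern.** Stratified blocks balance the arms on sex. That balance reduces the true variability of the treatment estimate if sex is related to the outcome given the other covariates. A model without sex does not see the reduction: it leaves the variance due to sex in the residual, so the reported standard error exceeds the true one. Confidence intervals are then a little too wide, the actual type I error falls below the nominal 5%, and some power is lost.

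Here the article itself gives an outcome-related reason for stratifying, then states an adjustment set that leaves the factor out. With about 37 evaluable patients per arm, it is reasonable to ask how much precision this could cost.

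**Working it through.** **Inputs from the article.** Difference 2%, SD of change 3%, two-sided 5% level, 80% power, 37 evaluable per group, 20% discontinuation, 1:1 allocation, stratified by sex.

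**Input not in the article.** The share of residual variance that sex explains once baseline ECM volume is in the model (partial R²). It is assumed below and varied.

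**Step 1: the plan's own figure.** The noncentral-t power for two means, with noncentrality 2 / (3 × √(2/n)), is 79.7% at n = 36 and 80.8% at n = 37. So 37 per group reproduces. Then 37 / 0.8 = 46.25, rounded up to 47 per group, and 2 × 47 = 94. The calculation uses the unadjusted SD of change.

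**Step 2: loss for a given partial R².** Take the residual SD without sex as 3%, which is conservative because it credits nothing to baseline ECM volume. With sex balanced across arms:
- the true residual SD is 3 × √(1 − R²);
- the model without sex still reports an SE based on SD 3, overstated by the factor 1/√(1 − R²);
- its effective critical value is the usual t value (71 df) times that factor; the model with sex has 70 df.

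| Partial R² of sex | SE overstated | Power without sex | Power with sex | Type I error without sex |
|---|---|---|---|---|
| 0 | 0% | 80.7% | 80.7% | 5.0% |
| 0.01 | 0.5% | 80.9% | 81.1% | 4.9% |
| 0.02 | 1.0% | 81.0% | 81.5% | 4.8% |
| 0.05 | 2.6% | 81.3% | 82.7% | 4.4% |
| 0.10 | 5.4% | 82.0% | 84.6% | 3.9% |

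A simulation of 5,000 trials per setting agreed in direction and approximate size. At R² = 0.10, power was 82.1% without sex and 84.6% with it. At R² = 0 it was 80.5% and 80.3%.

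**Step 3: what R² might be if the sex difference is stable.** Suppose the sexes differ by d points at both baseline and week 52, with an equal sex split and a within-sex between-patient SD of 2 to 4 points (all assumed). If the whole SD of change is visit-to-visit variation, its variance per visit is 3² / 2 = 4.5.

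Worked case, d = 2 and between-patient SD 3:
- Within sex, variance is 9 + 4.5 = 13.5 and covariance is 9. The slope is 9 / 13.5 = 0.667, so the sex effect left after baseline is (1 − 0.667) × 2 = 0.67 points.
- Residual variance with sex: 13.5 − 9² / 13.5 = 7.50 (SD 2.739).
- Without sex, the between-sex variance d²/4 = 1 joins both terms: 14.5 − 10² / 14.5 = 7.60 (SD 2.757).
- Partial R² = 0.0136, and the SE is overstated by 0.7%.

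Over d = 1 to 3 and SD 2 to 4, the partial R² runs from 0.0015 to 0.07 and the SE overstatement from 0.07% to 3.7%. Power is 85% to 91% either way, and the loss is about 0 to 2 points.

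**The case against.** The strongest reply is that the article's reason for stratifying concerns the level of ECM volume, and the ANCOVA already adjusts for that level. Nothing in the article says that sex predicts change in ECM volume, or week-52 ECM volume once baseline is known. If it does not, nothing is lost. This largely stands. It is not complete, because baseline is a single scan: if that scan measures a patient's ECM volume imperfectly, a stable sex difference leaves a residual, as in Step 3. That residual is modest.

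A second reply is that a condensed article need not list every covariate, that it does not call baseline ECM volume the sole one, and that the full protocol or SAP, not shown, may add sex. That also stands: the two sections do not contradict each other. Still, the article does state an adjustment set, and the stratification factor is not in it.

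Two stronger readings are tempting and unsupported:
- A reader might infer a serious loss. A simulation with an assumed residual SD of 2.6% and a 3-point residual sex effect gives 80% power without sex against 89% with it, and 2.7% type I error without it. But that model starts from a 1.5-point baseline gap with slope 0.7, so the gap at week 52 would be 0.7 × 1.5 + 3 = 4.05 points. The article suggests no such widening. A stable 1.5-point gap needs a residual effect of only 1.5 − 1.05 = 0.45, and simulations of that case put the loss at about 0.1 to 0.4 power points, with type I error near 5%. The larger figures are not expected values.
- A reader might infer that sex predicts the secondary outcomes too. The article states no sex difference for any of them, nor for PCr/ATP ratio.

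**Conclusion.** The point holds as a minor improvement to the model. Sex is the stratification factor and is absent from the stated adjustment sets. The consequence is conditional: the standard error is too large only if sex predicts week-52 ECM volume beyond baseline.

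Over the assumed ranges the cost is about 0 to 3 power points, probably towards the lower end, and nil without a residual effect. The planned 80% is not undermined, because it rests on the unadjusted SD of change and power without sex stays above 80% throughout the table. Any error is conservative, so a positive result would not be called into question. The size rests on partial R² values and sex differences that the article does not supply.

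**What to change.** State that the primary ANCOVA includes sex, the stratification factor, as a fixed effect together with baseline ECM volume. Use the same form in the other ANCOVA arm comparisons, including PCr/ATP ratio: the baseline value of the outcome plus sex. For those outcomes the reason is consistency with the randomisation, not a documented sex effect. If the full protocol or SAP already says this, no change is needed beyond making the published description agree.

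The cost is a few words and one degree of freedom (70 instead of 71 at 74 evaluable patients). Sex is already recorded for randomisation. With no residual sex effect, power is 80.7% with or without it, so there is no practical penalty.

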### Patients

The eligibility criteria are summarised in Table 2. Briefly, patients are ≥ 40 years of age, have a LVEF ≥ 45%, have symptoms and signs of HF and have B-type natriuretic peptide (BNP) ≥ 100 pg/ml or N-terminal pro-B-type natriuretic peptide (NT-proBNP) ≥ 300 pg/ml at baseline (patients in atrial fibrillation at baseline are required to have BNP ≥ 300 pg/ml or NT-proBNP ≥ 900 pg/ml). In addition, in order to be randomised, patients are required to have myocardial fibrosis, defined as an ECM volume ≥ 27% measured using CMR at Visit 0. An ECM volume threshold of 27% was chosen because it represents one standard deviation above that in healthy volunteers scanned at the host institution (Manchester University NHS Foundation Trust). Patients who meet eligibility criteria but who have an ECM volume < 27% are invited to take part in a sub-study (see below) and are entered into a registry. Key exclusion criteria include a probable alternative cause of patients’ symptoms and contraindications to CMR scanning or gadolinium-based contrast agent administration, including severe renal dysfunction, defined as an estimated glomerular filtration rate of < 30 mL/min.

**Table 2 Tab2:** Eligibility criteria

Inclusion criteria	
1. Written informed consent 2. Male or female, aged 40 years or older 3. HF, defined as one symptom present at the time of screening, and one sign present at the time of screening or in the previous 12 months. Symptoms and signs are defined as: Symptoms: dyspnoea on exertion, orthopnoea or paroxysmal nocturnal dyspnoea. Signs: peripheral oedema, crackles on chest auscultation post-cough, raised jugular venous pressure or chest x-ray demonstrating pleural effusion, pulmonary congestion, or cardiomegaly 4. LVEF ≥ 45% at visit 0, (any local LVEF measurement made using echocardiography or CMR). 5. BNP ≥ 100 pg/ml or NT-proBNP ≥ 300 pg/ml recorded at visit 0. For patients in atrial fibrillation on visit 0 ECG, BNP ≥ 300 pg/ml or NT-proBNP ≥ 900 pg/ml at visit 0. 6. In order to be randomised, patients must also have myocardial fibrosis, defined as ECM volume ≥ 27% by CMR at visit 0	
Exclusion criteria	

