### Sub-Study

Whilst myocardial fibrosis is an important pathophysiological mechanism in HFpEF, the mechanisms by which it exerts a deleterious effect are not clear. A widely held hypothesis is that myocardial fibrosis impairs myocyte capillary blood supply and causes arteriolar vasomotor dysfunction, which leads to energy starvation of cells and impaired energetics. Indeed, there is evidence of impaired myocardial energetics in HFpEF, but the relationship between ECM expansion and myocardial energy metabolism has not been investigated [52]. The hypotheses for the sub-study are (1) at baseline, myocardial ECM volume will be inversely associated with phosphocreatine (PCr) to adenosine triphosphate (ATP) ratio; and (2) pirfenidone-induced ECM regression will be associated with an improvement in PCr:ATP ratio.

PCr:ATP ratio will be measured at baseline using ^31^phosphorus magnetic resonance spectroscopy (^31^P MRS) in a subgroup of patients who are due to be randomised (i.e. all have an ECM volume ≥ 27%) and a subgroup of patients without ECM expansion (i.e. ECM volume < 27%) but who otherwise meet eligibility criteria, in order to assess the relationship between myocardial ECM volume and energetic status. ^31^P MRS will then be repeated in randomised patients after 52 weeks of treatment in order to compare the change in energetic status in the pirfenidone group with the change in energetic status in the placebo group. The relationships between myocardial ECM volume, energetic status and mechanical properties will be investigated. Details of the ^31^P MRS procedure are given in the Online Appendix.

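### The sub-study's baseline test of ECM volume against PCr/ATP names no adjustment for sex, although the article says ECM volume differs by sex

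*Protocol article*

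**What the plan says.** All references are to the protocol article.

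- **Sub-Study** gives the first hypothesis as "at baseline, myocardial ECM volume will be inversely associated with phosphocreatine (PCr) to adenosine triphosphate (ATP) ratio". This is a statement about a graded association. The comparison group is "a subgroup of patients without ECM expansion (i.e. ECM volume < 27%) but who otherwise meet eligibility criteria".
- **Patients** explains the cut-off: "An ECM volume threshold of 27% was chosen because it represents one standard deviation above that in healthy volunteers". One value serves both sexes.
- **Sub-Study Sample Size** sizes the baseline comparison on the two groups: "Thirty-three participants per group are required to detect an absolute minimum difference in PCr/ATP ratio of 0.37", with SD 0.52, 80% power and a two-sided 5% level.
- **Analysis** states the method: "PCr/ATP ratio and mechanical variables will be compared between patients with and without ECM expansion at baseline using an independent" *t* test, with transformation where needed. The next sentence adds: "Correlation analysis will be used to assess the relationships between PCr/ATP ratio, mechanics and ECM volume". No covariate is attached to either. The same section does name covariates elsewhere: baseline ECM volume for the main comparison, and baseline PCr/ATP for the randomised sub-study comparison.
- **Randomisation** stratifies by sex "because ECM volume is higher in females than males".

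**The concern.** Stratified randomisation balances sex between pirfenidone and placebo. It cannot balance sex between patients above and below 27%, because a patient's own ECM volume decides that membership. If women have higher ECM volume and both sexes share one cut-off, more women than men will tend to fall in the expanded group.

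If PCr/ATP, strain or torsion also differs by sex, part of an observed group difference would be a sex difference read as a fibrosis effect. With the opposite sign, a real association would be partly hidden. The correlation uses the full ECM scale, but without adjustment it mixes the same two sources. Neither stated analysis can separate fibrosis from sex, and the article presents the sub-study as mechanistic evidence that would support a phase III trial.

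A second, smaller matter is that the sizing and the first-named test use a dichotomy, whereas the hypothesis concerns a continuous relation.

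**Working it through.** **1. The article's own figure.** Inputs from Sub-Study Sample Size: difference 0.37, SD 0.52, 80% power, two-sided 5%.

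n per group = 2 × (1.960 + 0.842)² × (0.52 / 0.37)² = 31.0, rounded up to 32. The exact *t* calculation gives 31.99, so also 32. The stated 33 reproduces to within one patient. Power of the *t* test at 33 v 33 is 81.2%.

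**2. Sex mix of the two groups.** From the article: cut-off 27%; 63% of HFpEF patients at or above it (Sample Size); ECM volume higher in women. Assumed, because the article gives no figures: half the patients are women, ECM volume is normal with SD 4 within each sex, and the sex gap is 1, 2 or 3 points. The overall mean is set so that 63% lie at or above 27%. With equal numbers of each sex:

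- share of women, expanded group = P(women ≥ 27) / [P(women ≥ 27) + P(men ≥ 27)]
- share of women, non-expanded group = P(women < 27) / [P(women < 27) + P(men < 27)]

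| Assumed sex gap | P(≥ 27), women | P(≥ 27), men | Women, expanded | Women, non-expanded | Imbalance |
|---|---|---|---|---|---|
| 1 point | 0.677 | 0.583 | 54% | 44% | 10 points |
| 2 points | 0.723 | 0.537 | 57% | 37% | 20 points |
| 3 points | 0.768 | 0.492 | 61% | 31% | 30 points |

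The direction of the imbalance follows from the article's statement, given similar spread in both sexes. Its size is assumed.

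**3. Bias in the two-group contrast.** Bias = imbalance × sex difference in PCr/ATP. The article gives no sex difference, so a range from 0 to 0.3 is shown. The last column is the rejection rate of the *t* test at 33 v 33 when ECM volume has no effect.

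| Imbalance | Assumed sex difference | Bias | Share of 0.37 | Type I error |
|---|---|---|---|---|
| any | 0 | 0 | 0% | 5% |
| 0.10 | 0.3 | 0.03 | 8% | 5.6% |
| 0.20 | 0.2 | 0.04 | 11% | 6.1% |
| 0.20 | 0.3 | 0.06 | 16% | 7.5% |
| 0.30 | 0.3 | 0.09 | 24% | 10.6% |

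**4. Cost of the dichotomy.** This was simulated with 20,000 runs. ECM volume is normal, 63% lie above the cut, and PCr/ATP falls linearly with ECM volume. The slope is set so that the split yields exactly 0.37: the group means of standardised ECM volume are 0.599 and −1.020, so the slope is 0.37 / 1.620 = 0.228 per SD. The residual SD of 0.501 makes the pooled within-group SD 0.52.

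| Patients | *t* test | Continuous ECM volume |
|---|---|---|
| 33 v 33 | 81% | 95% |
| 66 v 33 | 91% | 99% |

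The second row applies if all 33 patients per treatment arm planned for the randomised comparison also enter the baseline comparison. On the continuous scale about 21 per group reach 80%.

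**5. Price of adjusting the two-group contrast for sex.** With about half the patients women, the variance rises by 1 / (1 − imbalance²). For imbalances of 0.10, 0.20 and 0.30 that is 1.010, 1.042 and 1.099, and power at 33 v 33 goes from 81.2% to 80.9%, 79.7% and 77.5%. This gives no credit for any residual variance that sex explains.

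**The case against.** Four points can be made for the plan.

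*Confounding is not shown.* It requires sex to be related to PCr/ATP as well as to ECM volume, and the article is silent on the former. This stands. A reader might infer that the association is confounded; the documents support only that it may be. Nothing in them links age or cardiac rhythm to ECM volume or to PCr/ATP either, so the case for those covariates is weaker than for sex.

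*Power is not wasted.* A reader might infer from the split at 27% that the sub-study is underpowered or discards the continuous information. It does neither. The *t* test meets its 80% target on the article's own inputs, and the correlation in the next sentence uses continuous ECM volume. What is left is that the test chosen for sizing is the less efficient of the two.

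*A condensed article may leave covariates to the full protocol or SAP.* This is fair as a general rule, and adjusted models may exist there. But the article does not leave the method open: it names a *t* test and a correlation, and it names covariates for the randomised comparisons in the same section. The point is about the stated method, not about missing detail.

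*The scope is small.* This stands. The comparison is a cross-sectional, secondary part of the sub-study. The primary endpoint does not depend on it, and the PCr/ATP treatment comparison is randomised and analysed by ANCOVA.

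**Conclusion.** The point holds as a minor one. The first sub-study hypothesis is tested by two analyses with no adjustment named, and one of them contrasts non-randomised groups formed by a cut-off that the article's own statement implies will sort patients partly by sex. The result may be confounded by sex.

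The size cannot be fixed from the documents. Over the assumed ranges (imbalance 10 to 30 points, sex difference in PCr/ATP 0 to 0.3) the bias runs from 0 to about 0.09, and the type I error from 5% to about 11%. Below the top of those ranges the effect is modest. The gain from 81% to 95% power rests on normal ECM volume and a linear relation, and the planned correlation already offers most of it. The case for change is therefore mainly the sex adjustment, with the match between test and hypothesis as a further benefit.

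**What to change.** In the sub-study paragraph of Analysis:

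- Make the main test of the first hypothesis a linear regression of PCr/ATP on continuous baseline ECM volume, adjusted for sex. Report the slope with its 95% confidence interval.
- Age and atrial fibrillation may be added if they are prespecified; they are optional.
- Give the expanded v non-expanded contrast, also adjusted for sex, as supportive.
- Use the same model for the mechanical variables.

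The cost is wording. Sex is the stratification factor, and age and the ECG are available at the baseline visit. The model spends a few degrees of freedom. The adjusted two-group contrast loses up to just under 4 points of power (81.2% to 77.5%) at a 30-point imbalance. The slope relies on linearity, which should be checked, and the two-group contrast gives a cross-check that does not need it. The sample size need not change.
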